### 2.8. Statistical Analyses

Statistical analyses will be performed at both national and cross-national levels. Data will be analyzed using intention-to-treat principles [119] and adjusted for cluster effect [62]. Baseline characteristics will be preliminarily compared to check equivalence between study groups using analysis of variance (ANOVA) and *χ*^2^ tests. To answer primary and secondary research questions, differences in primary and secondary outcomes between the study arms from T0 through T1 and T2 will be tested using linear mixed effect models. These analyses will be based on individual participant-level data, allowing for clustering between AYCs within the same school or geographical area [62,120]. Models will include the fixed effects of study arm, country and delivery approach, time and their interaction effects. The cluster will be considered as a random effect. Models will be adjusted for characteristics that are unbalanced between study arms and significantly associated with the outcome measures. In case of violations of assumptions underlying planned analyses (e.g., equal variance and normal distribution of residuals) appropriate mathematical transformations of raw scores (e.g., logarithmic scale) or robust estimation methods will be applied [121]. Interpretation of results will be based on both statistical significance (*p* < 0.05, two-tailed) and measures of effect size [122]. We will also summarize post-intervention self-assessment and process evaluation measures. Analysis of qualitative data in national languages (for control variables likes and dislikes about caring and for intervention acceptability) will be performed using content analysis [123].

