Two different methods will be followed in the delivery of the ME-WE intervention: a fully face-to-face approach (adopted by Italy, Slovenia and United Kingdom), and a blended approach that combines face-to-face and online sessions delivered via a dedicated ME-WE mobile app (adopted by Sweden, Switzerland and the Netherlands), which was codesigned with YCs at earlier stages of the ME-WE European project. Recent meta-analytic evidence supports the equivalence of face-to-face and web-mediated psychological interventions [66,67]. Both delivery approaches will address the same psychological processes and will use similar exercises and activities. The rationale for adopting two distinct approaches lies in different country characteristics with respect to the use of information and communication technologies. Indeed, recent data indicate that Sweden, Switzerland and the Netherlands rank among the highest in digital skills, with 72–79% of citizens having basic or above basic overall digital skills, while Italy and Slovenia rank among the lowest, with 42–55% [68]. Although United Kingdom ranks above average digital skills (74%), they opted for a face-to-face approach due to their prior experiences of running face-to-face groups in the context of YCs’ projects [69]. In the blended approach, sessions 1, 3, 7 and the 3 months follow-up meeting will be performed face-to-face, while sessions 2, 4, 5 and 6 will be performed online using the ME-WE app and the ZOOM platform. In the online sessions, the theoretical DNA-V inputs will be provided through short videos. The activities and exercises have been slightly modified to be easily performed online and remotely by participants, but facilitators will use the same instructions as in the fully face-to-face approach.

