#### 3.4.2. Evaluation of Online Delivery of the ME-WE Intervention

Satisfaction with the online delivery of the ME-WE intervention due to COVID-19 restrictions will be assessed. A Likert-type item (0 = totally dissatisfied to 10 = totally satisfied) will be administered, in addition to 3 multiple-choice items addressing satisfaction and dissatisfaction with specific features (e.g., user-friendliness and contents) and any problems encountered during the intervention delivery (e.g., network issues). Furthermore, participants will be asked how they felt about being part of a group (1 item, 5-point scale ranging from always to not at all). For groups that started face-to-face but then continued remotely due to COVID-19 outbreak amidst the intervention delivery, information on the perceived usefulness and enjoyability of online vs. face-to-face sessions will be also collected (2 items, 5-point scale ranging from always to not at all).

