
If the ME-WE intervention proves its superiority, an evidence-based primary prevention group intervention to support AYCs’ well-being during their transition into adulthood would be available in both face-to-face and online, app-mediated versions. Such an intervention could be implemented in educational and clinical settings, and educators together with health and social care professionals will have a new avenue for referral of AYCs available to them. The availability of an app-based version has the advantage of reducing stigma and enhancing anonymity that may prevent adolescents from accessing psychosocial support services and programs [132]. As well, it provides greater flexibility as it is not bound to a physical location. Further, group-based interventions can be more cost-effective than one-to-one interventions, and have the valuable potential to reduce isolation, promote peer-to-peer interactions and create bonds among AYCs, which has been reported as an unmet need of these youth [133]. From a research perspective, the outcomes of this study will contribute to evidence-based practices in primary prevention of psychosocial difficulties in AYCs. Additionally, if the ME-WE intervention is found to have an effect, this study will gather novel knowledge on the effectiveness of the DNA-V model [49] for promoting the mental health and well-being of middle adolescents who care for a family member or significant other.

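### The cross-national mixed model enters delivery approach beside country, with which it is aliased, and names no within-person term for T0, T1 and T2, which costs power on the arm-by-time test

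*Protocol article*

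**What the plan says.** Section 2.8 plans analyses at two levels: "Statistical analyses will be performed at both national and cross-national levels". For the main comparison, "differences in primary and secondary outcomes between the study arms from T0 through T1 and T2 will be tested using linear mixed effect models". The fixed part is given as: "Models will include the fixed effects of study arm, country and delivery approach, time and their interaction effects". The random part is one sentence: "The cluster will be considered as a random effect". The correlation the model is meant to handle is described as "allowing for clustering between AYCs within the same school or geographical area".

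Section 2.3 assigns delivery by country: "a fully face-to-face approach (adopted by Italy, Slovenia and United Kingdom), and a blended approach that combines face-to-face and online sessions", the blended approach being used in Sweden, Switzerland and the Netherlands. Section 3.3 moves both approaches online but keeps the same split: video-conferencing for Italy, Slovenia and the United Kingdom, and the app for the other three.

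Section 3.6 then separates the cross-national analysis. Italy, Slovenia, the Netherlands and the United Kingdom remain as cluster trials. Sweden and Switzerland are analysed by mixed ANOVA with arm, country and time and no delivery term. Section 3 keeps Section 2 in force wherever it is not changed, so the Section 2.8 term list still governs the four cluster countries.

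**The concern.** There are two problems in the same model statement.

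First, a factor that is constant within every country adds no information to a model that already contains country. Any delivery effect the software printed would depend on which redundant column it dropped. It would be a contrast between countries, not between modes of delivery. Section 5 says that, if the intervention succeeds, it "would be available in both face-to-face and online, app-mediated versions". A reader could take a printed delivery term as evidence on those versions, which this model cannot give.

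Second, the trial's question is whether change from T0 differs between arms. A model with a cluster effect and no participant effect or within-person covariance lets one adolescent's three visits correlate no more than visits of two different adolescents in the same cluster. Stable differences between adolescents then stay in the residual used to test arm-by-time, although they cancel from each adolescent's change. The test becomes less sensitive than the data allow.

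**Working it through.** The plan reports no figure of its own for either problem. Its nearest figure is the minimum of 24 per group in Section 2.7. That cannot be reproduced without knowing the test and the within-person correlation, which are not stated, and nothing below rests on it.

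**1. Aliasing.** The inputs are two arms, three visits, the countries, and the country-to-delivery map in Sections 2.3 and 3.3.

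- Main effects, six countries: 1 intercept + 1 arm + 2 time + 5 country + 1 delivery = 10 columns, rank 9. Four cluster countries: 1 + 1 + 2 + 3 + 1 = 8 columns, rank 7.
- With all arm and time products of country and of delivery, arm and time span 2 × 3 = 6 columns. Six countries: 6 × (1 + 5 + 1) = 42 columns, rank 6 × 6 = 36. Four countries: 6 × (1 + 3 + 1) = 30 columns, rank 6 × 4 = 24.
- With delivery removed: 36 columns and rank 36, or 24 columns and rank 24. Both have full rank.

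Delivery-by-arm-by-time is not estimable in either set. Arm-by-time averaged over the observed country cells is estimable in both. An average giving each delivery approach weight one half is estimable with six countries (split 3:3) but not with the four cluster countries (split 3:1). The weighting therefore needs care if the redundant term is left in.

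**2. Repeated measures.** The inputs are the intracluster correlation of 0.05 and power of 80% from Section 2.7, and the two-sided 5% level from Section 2.8. The within-person correlation ρ is an assumption, because the article gives none; the values used are 0.3, 0.5 and 0.7.

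With n adolescents per arm and outcome variance σ², the T1–T0 arm contrast has these variances:

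- true: 4σ²(1 − ρ)/n, because both the cluster and the participant effects cancel in the change;
- under the cluster-only model: 4σ²(1 − 0.05)/n, because only the cluster effect is removed.

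The standard error ratio is r = √[0.95/(1 − ρ)]. At 80% nominal power the standardised effect is 1.96 + 0.84 = 2.80, so actual power is Φ(2.80 − 1.96r).

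| Assumed ρ | r | 2.80 − 1.96r | Power, closed form | Power, simulated | Type I error, simulated |
|---|---|---|---|---|---|
| 0.3 | √(0.95/0.70) = 1.165 | 0.52 | 70% | 71% | 2.3–2.5% |
| 0.5 | √(0.95/0.50) = 1.378 | 0.10 | 54% | 55–56% | 0.8–1.0% |
| 0.7 | √(0.95/0.30) = 1.780 | −0.69 | 25% | 28% | 0.1% |

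The simulation used 20,000 replicates, balanced clusters (4 per arm of 8 adolescents, and 8 per arm of 10), an intracluster correlation of 0.05 and a critical value of 1.96. Adding a participant effect restored type I error to 4.95–5.3% and power to about 80%.

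**The case against.** Several defences deserve weight.

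- *The model can still be fitted.* A reader might infer that the whole model cannot be estimated. It can: the surplus columns are dropped and arm-by-time over the observed countries survives. Country and delivery are constant within a national analysis, so aliasing does not arise there. The Sweden and Switzerland mixed ANOVA omits delivery and handles repeated measures by construction, so neither point touches it. This defence stands and limits the first problem to the delivery terms of the cross-national model.
- *Country and delivery may be meant as one joint factor.* The wording allows this, but such a factor is simply country, so the delivery part is still redundant.
- *Actual mode did vary within countries.* Section 3.4.2 provides "For groups that started face-to-face but then continued remotely due to COVID-19 outbreak amidst the intervention delivery". However, Section 2.8 does not define delivery by actual mode or period, and the documents do not say that mode is recorded in a form that would support such coding.
- *A participant effect is not excluded, and an article may leave covariance detail to a fuller plan.* This is true in general. Here Section 5 says the article details the statistical analysis plan in order to prevent data-driven analysis, and the random part that it states has cluster alone. The robust methods in Section 2.8 are offered for problems such as unequal variance and non-normal residuals, not as a planned treatment of within-person dependence.
- *A delivery comparison is not a research question.* Correct. The Section 5 sentence concerns which versions would be available and does not compare them, so the risk there is one of interpretation.

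A reader might also infer inflated type I error for the arm main effect. Setting the variance of a three-visit mean, σ²(1 + 2ρ)/3, against σ²/3 would suggest about 17–21% at ρ of 0.5 to 0.7. That comparison describes a model with no random effect at all. With a cluster effect, arm is tested against between-cluster variation, which already contains the averaged participant variance. The simulated rejection rate was 7–9% and did not rise with ρ. It reflects normal critical values with few clusters.

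**Conclusion.** The point holds, and the model statement is wrong as written. In the cross-national model, delivery approach and its interactions are fully aliased with country, both as first planned and as amended; in the four-country model, delivery is the Netherlands indicator. This conclusion follows from the design and needs no assumption beyond the country-to-delivery map.

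The stated random part omits the participant level, which affects both the national and the cross-national analyses of the four cluster countries. The consequence is lost power on arm-by-time, not false positives. The standard error is too large by a factor of about 1.16, 1.38 or 1.78, and power is about 70%, 54–56% or 25–28% in place of 80%, at ρ of 0.3, 0.5 or 0.7. These sizes assume the protocol's intracluster correlation of 0.05, equal correlation between visits, cluster effects stable over time, and the illustrative values of ρ.

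**What to change.** Amend Sections 2.8 and 3.6 as follows.

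1. In the cross-national cluster model, keep country and remove delivery approach and its interactions. Alternatively, report delivery only as a descriptive contrast between countries, declared to be confounded with country.
2. State the random part as cluster plus participant nested in cluster, or as cluster plus an unstructured within-person covariance over T0, T1 and T2. Apply the within-person term in the national models of the cluster countries too.
3. Name arm-by-time as the test of the research question.
4. State that no conclusion will be drawn about one delivery version against another.

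The cost is analysis wording and one extra variance component to estimate (a few more parameters if the covariance is unstructured). No new data are needed. Coding delivery by actual mode or period would be an optional addition, and only if that information proves to have been recorded. Section 4 reports the trial as ongoing, so the change can be made before the final analysis.

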### 2.9. Ethics Approval

All participants will be involved in the study on a voluntary basis in accordance with the Declaration of Helsinki (1964; 2013) [124]. Informed consent will be sought from both AYCs and parents or legal guardians, in accordance with applicable national legislation and institutional guidance. Data will be processed in compliance with both national laws on data protection and the General Data Protection Regulation (GDPR) of the European Union (2016/679) [125] to guarantee the respondents’ anonymity and privacy. Formal ethics approval has been obtained from the Ethical Review boards of the University of Bologna (Italy), University of Ljubljana (Slovenia), University of Amsterdam, Faculty of Social Sciences (The Netherlands), University of Sussex (United Kingdom) and from the National Research Ethical Review Board (Sweden). According to the national human research act, the Ethics Committee of the Zürich Canton deemed formal ethical approval unnecessary.

## 3. COVID-19-Related Amendments to Study Protocol Methods

The COVID-19 pandemic has introduced important challenges to the continuation of this study. To avoid costly trial closures, deviations from the original study protocol were deemed unavoidable by the research project team and amendments were made to the originally planned methodology. To comply with the restrictions and precautionary measures introduced at national levels, the study has been virtualized on April 2020, including remote enrollment, screening, consent and data collection, and a fully online delivery of the ME-WE intervention and of training and supervision of facilitators [126,127]. COVID-19-related amendments to the study protocol methods are described in detail in the following subsections. If not specified below, the original study protocol as described in Section 2 will be followed.

### 3.1. Study Design Amendments

Sweden and Switzerland will turn to randomization of individual participants since their new recruitment method (see next section) does not pose a risk for spillover effects.

### 3.2. Participants

#### Recruitment Amendments

Due to COVID-related interruptions and slowing down of recruitment of trial participants, Sweden and Switzerland will launch national social media recruitment campaigns. In all six participating countries, recruitment and enrollment will be performed remotely, and screening interviews to assess eligibility of participants will be conducted exclusively by telephone or using video-conferencing applications (e.g., Microsoft Teams, ZOOM). Written parental (or guardian) and self-consent to be involved in the study will be collected by e-mail or recorded by Microsoft Teams (version 1.3) or ZOOM (version 5).

### 3.3. Intervention Amendments

In all six participating countries, new delivery methods will replace those originally planned for the ME-WE intervention. Specifically, fully face-to-face delivery (planned for Italy, Slovenia and United Kingdom) will be replaced by online sessions using video-conferencing instruments allowing for visual presentations of participants and session materials (e.g., Microsoft Teams and ZOOM). The blended delivery approach (planned for Sweden, Switzerland and the Netherlands) will be replaced solely by online meetings using the ME-WE mobile app and supported with the ZOOM video-conferencing system for all intervention sessions. In both delivery approaches, no changes will be introduced in the intervention contents. Some activities and exercises will be slightly adapted to fit the online delivery mode (Table S1).

Training and supervision of facilitators will be delivered fully online using video-conferencing platforms.

### 3.4. Outcome Measures Amendments

Assessments will be performed solely online, using the web-based version of the study questionnaires. Additional COVID-related measures will be included. Specifically, the perceived impact of the COVID-19 pandemic on everyday life and perceived mental health [128] will be assessed at all assessment points in both study groups. At T1 and T2, AYCs in the intervention group will be also asked for their experiences with participating in the ME-WE intervention during the pandemic and their evaluation of the online delivery mode.

#### 3.4.1. COVID-19-Related Control Variables

Three open-ended questions will ask AYCs for the impact of the COVID-19 pandemic on their lives and mental and physical health, and whether they or their families are receiving the support and services they need during the COVID-19 crisis. AYCs in the intervention group will receive a further open-ended question asking them how they experienced their participation in the ME-WE sessions and the exercises and home activities proposed in the ME-WE intervention during the COVID-19 pandemic.

#### 3.4.2. Evaluation of Online Delivery of the ME-WE Intervention

Satisfaction with the online delivery of the ME-WE intervention due to COVID-19 restrictions will be assessed. A Likert-type item (0 = totally dissatisfied to 10 = totally satisfied) will be administered, in addition to 3 multiple-choice items addressing satisfaction and dissatisfaction with specific features (e.g., user-friendliness and contents) and any problems encountered during the intervention delivery (e.g., network issues). Furthermore, participants will be asked how they felt about being part of a group (1 item, 5-point scale ranging from always to not at all). For groups that started face-to-face but then continued remotely due to COVID-19 outbreak amidst the intervention delivery, information on the perceived usefulness and enjoyability of online vs. face-to-face sessions will be also collected (2 items, 5-point scale ranging from always to not at all).

### 3.5. Sample Size Calculation Amendments

The minimum required sample size was revised for Sweden and Switzerland, since randomization in these countries will occur at the individual participant level. A minimum group size of 24 AYCs was established based on power analyses with a medium effect size, a power of 80% and an α-error probability of 5%. Compensating for attrition (20%), a minimum total sample size of 58 AYCs (29 AYCs in the intervention and 29 AYCs in the waitlist group) will be required in Sweden and Switzerland.

### 3.6. Statistical Analyses Amendments

For countries that turned to an individual-based RCT (i.e., Sweden and Switzerland), statistical analyses will be performed at the individual participant-level, with no cluster-based adjustment. Statistical analyses at the cross-national level will be performed separately for countries conducting cluster RCTs (i.e., Italy, Slovenia, the Netherlands and United Kingdom) and countries conducting individual-based RCTs (i.e., Sweden and Switzerland). For individual based RCTs, differences in primary and secondary outcomes between the study arms from T0 through T1 and T2 will be tested using mixed ANOVA. Models will include the effects of study arm, country, time and their interaction effects. In case of violations of assumptions underlying planned analyses, appropriate data transformations or robust estimation methods will be applied [121]. Analysis of qualitative data collected using newly added COVID-19-related open-ended questions in national languages would be performed using content analysis [123].

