### 2.3. Intervention

The ME-WE primary prevention intervention was developed by adjusting the existing DNA-V protocol [49] to the specific needs and experiences of AYCs aged 15–17. It was codesigned with YCs, former YCs and different types of professionals (e.g., psychologists, teachers, youth workers, health and social care professionals) in the framework of the blended learning networks (BLNs) performed at earlier stages of the ME-WE European project. BLNs are heterogeneous communities of practice that enable the voices of users and multistakeholders to be heard and that lead to shared learning [64]. In the ME-WE project, each country set up a BLN, which included between 8 and 14 participants (YCs, former YCs, professionals and representatives from non-governmental organizations) with the goal of contributing to the project implementation by providing their expert knowledge.

Participants of clusters allocated to the ME-WE intervention group will attend seven weekly 2-h group sessions, with a follow-up meeting after 3 months from the end of the intervention. Groups will be comprised of 5–10 AYCs. All sessions will have a similar structure (objectives, icebreaker, central activity/ies and final activity). After a first introductory session regarding the DNA-V model, sessions 2, 3 and 4 will introduce the advisor, noticer and discoverer metaphors, respectively. Session 5 will deal with values and values-oriented action and session 6 will attain psychological flexibility and self-compassion (i.e., the ability to approach personal suffering and failures with openness and awareness and showing self-kindness) [65]. The closing session 7 will focus on building strong social networks. At the end of sessions 2, 4, 5 and 6, participants will be provided with exercises to do at home, between one meeting and the next one, to practice the skills acquired during the session in everyday life. In the follow-up session, participants will reinforce the skills learned and discuss their experiences with the intervention. Table A1 provides a session-by-session outline of the ME-WE intervention contents.

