In both delivery approaches, two facilitators will conduct each session. Facilitators will be psychologists, youth workers, teachers, school nurses and carer support workers, all with solid experiences in working with groups and with young people. All facilitators will be trained in the ME-WE intervention before conducting the sessions, including information on the theoretical background of the DNA-V model and training sessions on the ME-WE intervention exercises that use a role-play technique. Facilitators will also be provided with both the DNA-V protocol manual and/or training course [70] and the ME-WE intervention manual (translated from English into local languages by local team members who are fluent in English). Throughout the study duration, they will be provided with ongoing supervision.

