### 2.7. Sample Size Calculation

For the primary outcome variables, a moderate effect size (*f* = 0.25) was pursued based on previous evidence in RCTs using ACT-based interventions [56,84,112]. A minimum group size of 24 AYCs was established based on power analyses with a power of 80% and an α-error probability of 5%. However, in the case of cluster RCTs, an effective sample size is in fact lower than that suggested by the actual number of participants due to observations on participants in the same cluster tending to be correlated [62]. Thus, initial sample size estimation (performed as if randomization occurred at the individual level) was corrected taking into account randomization occurring at the cluster level. For each country, an average cluster size was estimated using the formula for sample size determination in a finite population [113] and assuming the prevalence rate of AYCs in the population of adolescents aged 15–17 in that country. Based on available data, the estimated prevalence rate of YCs is about 3% in Italy [114], 7% in Sweden [115], about 8% in Switzerland [3], 6% in the Netherlands [116] and in the United Kingdom approximately 7% of all children are engaged in a high amount of caring and 3% in a very high amount [117], while no estimation is available yet for Slovenia. As Italy and Slovenia have both been classified as countries at the initial stage of awareness concerning AYCs [118], the Italian prevalence rate was also applied in the Slovenian sample size calculation. A design effect was then calculated using the average cluster size and an assumed intracluster correlation of 0.05. This design effect was multiplied by the initial sample size to obtain a sample size corrected for the cluster-based design, which was further increased by 20% to compensate for attrition. The minimum total sample sizes obtained from this procedure were as follows: 80 AYCs (40 AYCs in the intervention and 40 AYCs in the waitlist group) in Italy and Sweden, 76 AYCs (38 AYCs in the intervention and 38 AYCs in the waitlist group) in Slovenia, 102 AYCs (51 AYCs in the intervention and 51 AYCs in the waitlist group) in Switzerland, 112 AYCs in the Netherlands (56 AYCs in the intervention and 56 AYCs in the waitlist group) and 142 AYCs (71 AYCs in the intervention and 71 AYCs in the waitlist group) in the United Kingdom.

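### Sweden and Switzerland: the amended analysis and sample size ignore correlation within ME-WE delivery groups, so the arm-by-time test runs above its nominal 5% for any positive group correlation

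*Protocol article*

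**What the plan says.** Section 3.1 moves Sweden and Switzerland to individual randomisation because the new recruitment route carries no spillover risk. For these countries section 3.6 states that "statistical analyses will be performed at the individual participant-level, with no cluster-based adjustment", and it specifies a mixed ANOVA with arm, country, time and their interactions. There is no term for delivery group. Section 3.5 follows the same logic: "The minimum required sample size was revised for Sweden and Switzerland, since randomization in these countries will occur at the individual participant level". It continues "A minimum group size of 24 AYCs was established based on power analyses", raised by 20% for attrition to 29 per arm and 58 in total per country, with no design effect.

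The intervention remains a group programme. Section 2.3 says "Groups will be comprised of 5–10 AYCs" and that "two facilitators will conduct each session". Section 3 keeps the original methods wherever no change is specified. Section 3.3 changes the delivery medium only, and section 3.4.2 still asks participants how they felt about being part of a group.

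**The concern.** The reason given for individual randomisation, absence of spillover, concerns contamination between arms. It does not address correlation among participants who go through seven two-hour sessions with the same peers and facilitators. The programme intends such shared influence: in Table A1, session 7 presents the group as a resource, and social support is a primary outcome. The article allows an ICC of 0.05 for adolescents who share only a school or an area (section 2.7), but in effect zero for those who share the treatment itself.

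This is a partially nested design. Differences between delivery groups enter the arm contrast but not the error term of the mixed ANOVA. If they are positive, p-values and confidence intervals are too favourable in the Swedish analysis, the Swiss analysis and the cross-national analysis that combines the two. The 80% power figure was also set as if all observations were independent.

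**Working it through.** **Inputs from the article.** 24 evaluable per arm, 20% attrition, 29 per arm recruited (3.5); groups of 5–10 (2.3); f = 0.25 (2.7); two-sided 5% level (2.8); ICC 0.05, given for schools and areas only (2.7).

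**Assumed.** ICC for delivery groups, 0.01–0.10; within-person correlation ρ, 0.5–0.7, for the error rates.

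**1. The plan's own figure.** 24 × 1.20 = 28.8, so 29 per arm and 58 in total. This reproduces.

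**2. Number of groups.** 29/10 = 2.9 and 29/5 = 5.8, so about 3 to 6 ME-WE groups per country.

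**3. Variance of the arm difference.** The intervention-arm design effect is DE = 1 + (m − 1) × ICC. With no clustering in controls, the variance of the difference is multiplied by V = (1 + DE)/2. At ICC 0.05:
- m = 5: DE = 1 + 4 × 0.05 = 1.20, V = 1.10
- m = 10: DE = 1 + 9 × 0.05 = 1.45, V = 1.225

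**4. True error, large-sample formula.** Error = 2 × [1 − Φ(1.96/√V)].
- V = 1.10: 1.96/1.049 = 1.87, error 6.2%
- V = 1.225: 1.96/1.107 = 1.77, error 7.7%

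The same formula gives 5.2–5.5% at ICC 0.01 and 7.4–10.4% at ICC 0.10.

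**5. Simulation of the section 3.6 test.** Two arms, three waves, mixed ANOVA arm-by-time test, group effect added at T1 and T2 in the intervention arm only, ρ = 0.5 and 0.7:

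| Group ICC | True error per country |
|---|---|
| 0 (check) | about 5% |
| 0.01–0.02 | about 5–6% |
| 0.05 | about 6–9% with 29 per arm; about 6–8% with 24 evaluable |
| 0.10 | about 7–14% |

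The top of each range combines the largest groups with ρ = 0.7. A higher ρ makes matters worse because the test uses within-person change. The variance of change is 2(1 − ρ), which is 1.0 at ρ = 0.5 and 0.6 at ρ = 0.7. The same group variance of 0.05 therefore weighs 0.05/0.6 = 0.083 at the higher value. Pooling the two countries does not help: six intervention groups of eight gave 7.2–8.5% at ICC 0.05.

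**6. Power, if 24 per arm is exactly the 80% minimum.** Power = Φ[(1.96 + 0.84)/√V − 1.96].
- V = 1.10: 76%
- V = 1.225: 72%

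With group sizes after attrition (24/6 = 4 and 24/3 = 8), V = 1.075 and 1.175, giving 77% and 73%. The range is thus 72–77%, before any loss of degrees of freedom from having few groups.

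**7. Is 24 per arm the 80% minimum?** For the arm-by-time test with N = 48 and three waves, λ = N × f² × 3/(1 − ρ):
- ρ = 0.1: λ = 10, power 80.2%
- ρ = 0.5: λ = 18, power 97.0%
- ρ = 0.7: λ = 30, power 99.9%

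Only a ρ near 0.1 returns 80% for this test, and the article states neither the test nor ρ.

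**The case against.** The strongest counter-argument concerns size. No ICC for delivery groups is given, and the 0.05 describes schools and areas. At 0.01–0.02 the excess error is at most slight. The upper figures need three large groups, ρ = 0.7 and a group effect that persists in full to T2. All of this stands, and it is why the size is given as a range. The treatment effect estimate also remains unbiased; the problem lies in its standard error.

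A reader might infer that the trial misses its 80% power. The documents do not support that. At the within-person correlations used for the error rates, the arm-by-time test would start at 97–99.9% under independence (step 7), so the 72–77% holds only if the article's 24 is taken at face value as an exact minimum.

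A reader might also picture closed groups set against wholly independent controls. The article never calls the groups closed. Section 2.4 gives waitlist participants ice-breaker and team-building activities at three assessment meetings, and section 3.4 moves assessments online without saying whether those activities continue. That exposure is far smaller than seven treatment sessions, but it should not be assumed to be zero.

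Finally, sections 2.8 and 3.6 allow transformations or robust methods when assumptions fail. The examples in 2.8 are unequal variance and non-normal residuals. Transformation does not cure dependence, and 3.6 itself excludes cluster adjustment.

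**Conclusion.** The point holds. Section 3.6 makes an explicit analysis choice that is wrong for a group-delivered treatment, and nothing else in the article offsets it. The direction needs only a positive within-group correlation; the size is moderate and depends on the assumed ICC, from near nil at 0.01 to clearly material at 0.10. Two of six national analyses and one of two cross-national analyses are affected. On power, the supportable statement is that the 80% takes no account of within-group correlation. A definite shortfall is not established.

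**What to change.** In section 3.6, replace the exclusion of cluster adjustment with a linear mixed model that has a random effect for ME-WE delivery group in the intervention arm at T1 and T2, with Satterthwaite or Kenward–Roger degrees of freedom. Treat controls as single units, or group them by assessment meeting if the section 2.4 meetings are kept. Record a group ID for every intervention participant.

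In section 3.5, say that the 80% assumes no within-group correlation. Name the test and the within-person correlation behind the 24 per arm, and give the power of 58 over a range of group ICCs, for example 0.01–0.10.

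The cost is wording, one variance term and one recorded variable. Confidence intervals will be somewhat wider and the stated power less favourable. With about 3–6 groups per country, the variance component will be imprecisely estimated. No extra participants are needed.
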